# Efficacy of intermittent Theta Burst Stimulation (iTBS) and 10-Hz high-frequency repetitive transcranial magnetic stimulation (rTMS) in treatment-resistant unipolar depression: study protocol for a randomised controlled trial

**DOI:** 10.1186/s13063-016-1764-8

**Published:** 2017-01-13

**Keywords:** Repetitive transcranial magnetic stimulation (rTMS), Intermittent Theta Burst Stimulation (iTBS), Treatment-resistant depression, Relapse

## Abstract

**Background:**

The treatment of depression remains a challenge since at least 40% of patients do not respond to initial antidepressant therapy and 20% present chronic symptoms (more than 2 years despite standard treatment administered correctly). Repetitive transcranial magnetic stimulation (rTMS) is an effective adjuvant therapy but still not ideal. Intermittent Theta Burst Stimulation (iTBS), which has only been used recently in clinical practice, could have a faster and more intense effect compared to conventional protocols, including 10-Hz high-frequency rTMS (HF-rTMS). However, no controlled study has so far highlighted the superiority of iTBS in resistant unipolar depression.

**Methods/design:**

This paper focuses on the design of a randomised, controlled, double-blind, single-centre study with two parallel arms, carried out in France, in an attempt to assess the efficacy of an iTBS protocol versus a standard HF- rTMS protocol. Sixty patients aged between 18 and 75 years of age will be enrolled. They must be diagnosed with major depressive disorder persisting despite treatment with two antidepressants at an effective dose over a period of 6 weeks during the current episode. The study will consist of two phases: a treatment phase comprising 20 sessions of rTMS to the left dorsolateral prefrontal cortex, localised via a neuronavigation system and a 6-month longitudinal follow-up. The primary endpoint will be the number of responders per group, defined by a decrease of at least 50% in the initial score on the Montgomery and Asberg Rating Scale (MADRS) at the end of rTMS sessions. The secondary endpoints will be: response rate 1 month after rTMS sessions; number of remissions defined by a MADRS score of <8 at the endpoint and 1 month after; the number of responses and remissions maintained over the next 6 months; quality of life; and the presence of predictive markers of the therapeutic response: clinical (dimensional scales), neuropsychological (evaluation of cognitive functions), motor (objective motor testing) and neurophysiological (cortical excitability measurements).

**Discussion:**

The purpose of our study is to check the assumption of iTBS superiority in the management of unipolar depression and we will discuss its effect over time. In case of a significant increase in the number of therapeutic responses with a prolonged effect, the iTBS protocol could be considered a first-line protocol in resistant unipolar depression.

**Trial registration:**

ClinicalTrials.gov, Identifier NCT02376491. Registered on 17 February 2015 at http://clinicaltrials.gov.

**Electronic supplementary material:**

The online version of this article (doi:10.1186/s13063-016-1764-8) contains supplementary material, which is available to authorized users.

## Background

Depression is a real public health problem. In 2020, according to the World Health Organisation (WHO), depression will be the second major cause of handicap and premature death in the world after coronary diseases. Standard treatment comprises support therapy combined with medication. However, at least 40% of patients do not respond to the initial treatment and 20% present with persistent resistance to conventional pharmacological treatments [1]. It is, therefore, essential to find efficient treatment alternatives for resistant depression. The reference treatment in this case is still electroconvulsive therapy (ECT) with a 48% response rate in the event of severe resistance to pharmacological therapies [2]. Repetitive transcranial magnetic stimulation (rTMS) is a non-invasive, focal, cortical stimulation technique involving modulation of cortical excitability. It is an upstream alternative to ECT and could close to match comparable efficacy in the absence of psychotic symptoms with a satisfactory duration and number of stimuli [3, 4]. Its interest in the treatment of resistant unipolar depression has clearly been established in conjunction with antidepressant chemotherapy.

The efficacy of rTMS depends on its parameters (stimulation site, orientation of the magnetic field, number of stimuli delivered as well as the frequency, intensity and duration of stimulation) [5]. The two types of dorsolateral prefrontal cortex (DLPFC) stimulation used in the treatment of depression – high frequency to the left (L-HF) and low frequency to the right (R-LF) – have proved to be equi-effective [6–9]. Response rates on average vary from 30 to 40% depending on the series [10, 11], with a 58% response rate maintained at 3 months, then 33% at 6 months [12, 13].

Although these various parameters currently have yet to be optimised, a new rTMS technique known as Theta Burst Stimulation (TBS) has recently emerged. This displays faster, more robust action compared to conventional protocols [14], with excellent tolerability [15], provided that safety recommendations are followed [16]. Two different methods have been described: intermittent (iTBS) and continuous Theta Burst Stimulation (cTBS) with facilitating and inhibitory effects, respectively. iTBS involves the application of bursts of three pulses at a frequency of 50 Hz every 200 ms; therefore, at 5 Hz, delivery is over 2 s and repeated every 10 s, 20 times in succession. An uncontrolled study on a small sample generated 70% of responses and 42% of remissions in resistant unipolar depression following a course of iTBS [17]. These shorter sessions would be an additional source of comfort for the patient not to mention the lower cost of the session. It should be noted that a very recent study highlighted the superiority of iTBS over cTBS and placebo in the management of resistant depression [18]. In 2014, Bakker et al. demonstrated similar efficacy with iTBS prefrontal dorsomedial bilateral stimulation (6 min) and a 10-Hz protocol (30 min) in an uncontrolled retrospective study [19]. With regard to recent scientific literature, various points must be specifically investigated: controlled comparison of protocols with the enrolment of a homogeneous population in terms of treatment and clinical form of the condition (most studies combine both bipolar and unipolar disorder); duration of the effect with longitudinal follow-up; and predictive response factors [20]. The main predictive therapeutic response factors identified to date are age, duration of the episode, degree of therapeutic resistance, clinical profile and, in particular, cognitive impairment and psychomotor retardation [21, 22]. A study of cortical excitability, which reflects the gabaergic and glutamatergic transmission of cortical interneurones (IN), could also prove promising in distinguishing neurostimulation responder profiles. No controlled study comparing the efficacy of iTBS versus conventional rTMS protocols in unipolar resistant depression has been published to date.

### Specific aims

The aim of this randomised controlled trial is to investigate the efficacy of iTBS versus 10-Hz high-frequency transcranial magnetic stimulation (HF-rTMS) in a population of patients suffering from unipolar depression (Montgomery and Asberg Rating Scale (MADRS) score of >20) despite the use of two antidepressant agents during the current episode. Moreover, this trial will evaluate whether certain specific clinical or neuropsychological dimensions, objective measurements of psychomotor retardation or even distinct cortical excitability profiles could predict the efficacy of iTBS and HF-rTMS, respectively.

## Methods/design

### Study design, setting and recruitment

This is a randomised, controlled, double-blind, single-centre study. It is carried out at the Centre Hospitalier Universitaire (University Hospital Centre) of Nantes, France. The patients are randomly assigned to the iTBS or the HF-rTMS group as shown in Fig. 1 (Flow Chart). More specifically, the two parallel arms compare an iTBS protocol to a so-called conventional protocol at 10 Hz [23]. The stimulation target is identical in the left dorsolateral prefrontal cortex (Brodmann areas 9 and 46), localised via Nextim® (software Eximia®) neuronavigation. Participants are randomised to one of the treatment groups using a computer programme included in the electronic Case Report Form (e-CRF). This study has been approved by the local Nantes Ouest IV Ethics Committee (reference: ID RCB N°2014-AO1918-39) and compiled in accordance with the principles of the Declaration of Helsinki (final version 2004) as well as French legislation (article L1121-160 and L1126-7 of the Public Health Code). Additional quality standards are detailed in Additional file 1 according to SPIRIT Check-list requirements. All of the patients are given written and verbal information about the study aim and procedures. They sign a written Consent Form in order to take part in the study. The aim is to enrol 60 patients who have been put forward either by private or hospital psychiatrists in the region, previously informed in writing of the study.

**Fig. 1 Fig1:**
[figure not shown]
Flow Chart

### Inclusion criteria

The 60 patients between 18 and 75 years old must present with a current depressive episode considered major (defined by *Diagnostic and Statistical Manual of Mental Disorders*, *fifth edition* (DSM-V) diagnostic criteria [24] and a MADRS score of >20 [25]) and resistant (failure to respond to two sequences of different antidepressants at an effective dose level over a period of 6 weeks during the current episode). The current antidepressant is continued at a stable dose throughout the study.

Each subject must be able to: understand the information; take a decision; volunteer to participate; complete the required questionnaires; take orally administered treatment independently or have the necessary assistance to do so throughout the study; and return to the research centre for successive visits.

### Noninclusion criteria

Patients presenting with at least one of the following criteria are not be enrolled in the study: diagnosis of a bipolar disorder; schizophrenia; addiction; neurodegenerative disease; use of benzodiazepines (unless prescribed over 3 months earlier at a stable dosage); use of mood-modifying treatments (thyroid extracts, interferon, corticosteroids); previous failure of ECT therapy; anticonvulsant treatment; contraindication to magnetic resonance imaging (MRI); contraindication to the practice of rTMS: history of convulsions, progressive neurological and neurosurgical disorders; any prosthetic material or foreign body in situ (pacemaker, implantable defibrillator); minors or persons deprived of liberty following a legal or administrative decision or hospitalised without consent, in guardianship; or pregnant women or women of child-bearing age who are not using contraception because of no available data about iTBS and pregnancy (these women could receive, if absolutely necessary, from case to case, conventional rTMS treatment, outside the study). The same applies for subjects unable to guarantee longitudinal follow-up.

In case of a serious adverse event or exacerbated symptoms of depression, blind status will be lifted and patients will receive appropriate care and retained in the follow-up.

### Study process

The screening visit V1 (D − 21 to D42) includes the Patient Information Leaflet, collection of the Consent Form and checking of inclusion/exclusion criteria. The medical research team will be in charge of enrolment and assignation of participants to the intervention. The study manager and psychiatrist investigators can generate the allocation sequence. Treatment is adjusted in line with the course of therapy. A clinical examination is also carried out and MRI prescribed to rule out any neurological disorder and mark the neuronavigation target during the baseline visit. The procedure is conducted using a Siemens 1.5 T machine with the following sequences: diffusion, T1 3D, FLAIR 2D and T2 rapid and SWI.

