#### Randomisation

During the baseline inclusion visit, the inclusion/exclusion criteria are checked and participants randomised into two groups by a computerised random number generator with a permuted block design (ratio 1:1) without stratification or minimisation. Block size and type of variation (fixed or randomly) are not yet known by the investigators to maintain adequate blinding. Randomisation occurs in a recorded delay of maximum 72 h before first rTMS session.

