#### Blinding

Research nurses, who perform rTMS sessions, are the only persons to know the allocated sequence. Just after the randomisation, they will receive an automatic e-mail on their individual professional mail box. The session will take place in a dedicated room with appropriate noise control and a signal on the door during the session to prevent accidental entry of investigators. Patients are not told the group they belong to, will not have precise description of rTMS parameters and duration and will not be able to speak to each other. Both treatments will be equally presented as efficient and superior to placebo.

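### As worded, the protocol lets psychiatrist investigators generate the allocation sequence, contradicting its own statements on block size and on who knows the sequence

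*Protocol article*

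**What the plan says.** Four sections of the protocol article bear on who controls and who knows the allocation.

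- **Study process** covers enrolment first: "The medical research team will be in charge of enrolment and assignation of participants to the intervention". The next sentence reads: "The study manager and psychiatrist investigators can generate the allocation sequence".
- **Randomisation** describes assignment "by a computerised random number generator with a permuted block design (ratio 1:1) without stratification or minimisation". It adds: "Block size and type of variation (fixed or randomly) are not yet known by the investigators to maintain adequate blinding".
- **Blinding** says: "Research nurses, who perform rTMS sessions, are the only persons to know the allocated sequence". The release of each allocation follows: "Just after the randomisation, they will receive an automatic e-mail on their individual professional mail box". Investigators are also kept away from treatment by "a signal on the door during the session to prevent accidental entry of investigators".
- **Study design, setting and recruitment** places the randomisation in a programme within the e-CRF and describes the trial as double-blind and single-centre.

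**The concern.** Someone who generates a permuted-block sequence has its block scheme and its order. The protocol treats investigators' ignorance of the block scheme as necessary for blinding, yet assigns them the task that would reveal it. It also restricts knowledge of the sequence to the nurses, yet names two other parties, the study manager and the psychiatrist investigators, as able to produce it.

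Two protections are at stake. One is allocation concealment: a person who knows the next allocation can bring forward, delay or decline a patient accordingly. The other is investigator blinding. Neither kind of bias can be reliably removed in the analysis. With one centre and no stratification, a single list would govern every patient.

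**Working it through.** No figure in the plan depends on this point, and correcting it leaves the sample size of 60 unchanged. The check is therefore a comparison of statements, followed by an illustration of scale.

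**Step 1. Literal reading.** Take the Study process sentence at face value: an investigator generates the sequence.

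| Statement elsewhere | Can it hold as well? |
|---|---|
| Randomisation: investigators do not know block size or type of variation | No. The generator of a permuted-block list has both. |
| Blinding: only the nurses know the allocated sequence | No. The generator has the whole sequence. |
| Study design and Randomisation: computer-generated, in the e-CRF | Yes. A computer method does not say who sets up the list or who can view it. |

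Two statements fail under this reading.

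**Step 2. Alternative reading.** Suppose that generating the sequence means launching the e-CRF randomisation for one patient. The computer then produces the allocation, the nurses are notified by e-mail, and the investigator sees neither list nor result. All the statements can then hold. The Study process sentence does not say this, however. The sentence before it already covers assignment, so this one reads as a separate task. No sentence says that the list is hidden from investigators or names an independent person who produces it. The words "Block size and type of variation (fixed or randomly) are not yet known by the investigators to maintain adequate blinding" say *not yet*, which does not rule out later disclosure.

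**Step 3. Scale, for illustration only.** The article does not give the block size, so the sizes below are assumptions.

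- *Holding the list:* 60 of 60 allocations are known, or 100%.
- *Knowing a fixed block size and all past allocations:* an allocation is certain once one arm's quota in the block is used up. For a block of 4 at 1:1, the fourth allocation is always certain. The third is certain if the first two were equal. Of the six possible orders, two begin with equal pairs, so that probability is 2/6 = 1/3. The expected number of certain allocations per block is 1 + 1/3 = 4/3, and (4/3)/4 = 33%. Over 60 patients that is 15 blocks × 4/3 = 20 allocations.
- *Other assumed fixed sizes:* enumerating all orders gives 50% for blocks of 2, 25% for blocks of 6 and 20% for blocks of 8.
- *Knowing the block size alone:* no allocation is certain, because the earlier allocations in the block are needed as well, and the Blinding section gives those to the nurses only.

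**The case against.** The strongest reply is that the mechanism is described consistently elsewhere: e-CRF randomisation, a block scheme kept from investigators, and notification of the nurses after each randomisation. Against this stands one sentence, placed directly after a sentence on enrolment and assignment. It may be loose wording for being authorised to launch the randomisation. The supplementary SPIRIT checklist cited in the article is not shown and may be clearer. This reply stands as far as it goes: the harmless reading is plausible. It does not remove the conflict, which lies in what the article positively states and not in a detail left to a fuller document.

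A reader might infer three stronger things that the article does not support.

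- *That concealment has already failed.* Nothing shows that an investigator generated or saw the list.
- *That the psychiatrist investigators are the people who enrol.* Enrolment is given to the medical research team, which is not defined further. That the psychiatrists belong to it is likely but not stated.
- *That the primary endpoint is rated by the people who may generate the list.* The MADRS is not among the self-reported scales listed under Assessments, so it appears to be observer-rated. No rater is named for the end of the rTMS sessions. The Follow-up section has investigators meeting participants 1, 3 and 6 months after the last session, which is later than the primary endpoint.

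For these reasons no size of bias on the response rate can be derived from the document.

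**Conclusion.** The Study process sentence, as worded, is incompatible with the Randomisation and Blinding sections. How serious this is depends on which reading is true. If investigators only trigger the e-CRF module and cannot see list, block scheme or result, it is a wording error. If they do generate or hold the list, concealment and investigator blinding are defeated for every allocation on it, in a trial where one list serves all 60 patients. The document does not decide between the two, so the sponsor must.

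The 33% figure rests on an assumed fixed block of 4 and on knowledge of all past allocations. It shows scale, and the contradiction does not depend on it. The point should be settled before further patients are randomised, because the possible harm is severe and the correction is small.

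**What to change.** Replace the sentence in Study process with one that states the following:

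- The sequence is generated by a data manager or statistician with no role in recruitment, treatment or rating, and is held only in the e-CRF module.
- Investigators and the study manager may only request the next allocation, after eligibility is confirmed.
- The list, the block scheme and the result are hidden from them.

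In Randomisation, drop the word *yet*, so that the block scheme is withheld without a time limit.

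The Trial status section says recruitment is ongoing, so check now who has, or has had, access to the list and the block settings in the e-CRF. Only if an investigator did generate or see the list, regenerate the unused part under the new arrangement and report this with the results.

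The cost is protocol wording and an access-rights check. No extra patients are needed, and the planned sample size and analysis stay as they are.

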#### Randomisation

During the baseline inclusion visit, the inclusion/exclusion criteria are checked and participants randomised into two groups by a computerised random number generator with a permuted block design (ratio 1:1) without stratification or minimisation. Block size and type of variation (fixed or randomly) are not yet known by the investigators to maintain adequate blinding. Randomisation occurs in a recorded delay of maximum 72 h before first rTMS session.

#### Blinding

Research nurses, who perform rTMS sessions, are the only persons to know the allocated sequence. Just after the randomisation, they will receive an automatic e-mail on their individual professional mail box. The session will take place in a dedicated room with appropriate noise control and a signal on the door during the session to prevent accidental entry of investigators. Patients are not told the group they belong to, will not have precise description of rTMS parameters and duration and will not be able to speak to each other. Both treatments will be equally presented as efficient and superior to placebo.

#### Follow-up

Investigators will meet participants 1, 3 and 6 months after the last rTMS session.

A patient who fails to respond to therapy (no decrease of over 50% in the MADRS score) despite 4 weeks of treatment will continue longitudinal follow-up in order to avoid selection bias. A telephone call is made in the second, fourth and fifth month outside the follow-up consultations to keep in contact with patients and remind them of the next appointment in order to avoid their being lost to follow-up.

The study will last 33 months in total with 24 months being the enrolment period. Patients are followed up over a period of approximately 34 weeks in total (Table 1).

**Table 1 Tab1:** Flow chart

Clinical trial										
Study period	Pre-enrolment	Inclusion and randomisation	Trial period							
			rTMS treatment					Follow-up phase		
Clinical visits	V1 information	V2 (D − 3)	V3 AD0 Start of rTMS treatment	V4 D7 (±2D) After 5 sessions	V5 D14 (±2D) After 10 sessions	V6 D21 (±2D) After 15 sessions	V7 D28 (±2D) After 20 sessions	V8 M1 (±7D)	V9 M3 (±7D)	V10 M6 (±7D)
Length of time compared to randomisation	−21 to 42 days	0								
Inclusion/exclusion criteria	X	X	X	X	X	X				
Signed Consent Form	X	Verification								
Medical history	X									
MRI	X	Target labelling								
Concomitant treatments	X	X	X	X	X	X	X	X	X	X
Motor threshold titration			X	X	X	X	X			
Routine clinical examination	X	X	X	X	X	X	X	X	X	X
MADRS, CGI, BDI		X		X	X	X	X	X	X	X
SAS, SHAPS, MoCA, ERD, HARD		X					X	X		
MSM, TCI		X								
TMT MCST Verbal fluency		X					X	X		
FTT Prehensile motor strength Reaction times		X					X	X		
SF-36		X					X	X	X	X
Adverse events			X	X	X	X	X	X	X	X
Ancillary cortical excitability study										
Biophysical measurements			X				X			
Signed Consent Form	X	Verification								

*BDI* Beck Depression Inventory, *CGI* Clinical Global Impression, *ERD* Echelle de Ralentissement Dépressif, *FTT* Finger Taping Test, *HARD scale* Humeur, Anxiété, Ralentissement, Danger, *MADRS* Montgomery and Adsberg Rating Scale, *MCST* Modified Card Sorting Test, *MoCA* Montreal Cognitive Assessment, *MRI* magnetic resonance imaging, *MSM* Maudsley Staging Model, *rTMS* repetitive transcranial magnetic stimulation, *SAS* Starkstein’s Apathy Scale, *SF-36* Short-Form 36, *SHAPS* Snaith-Hamilton Pleasure Scale, *TCI* Temperament and Character Inventory, *TMT* Trail Making Test

